# Impact of Motivational Interviewing on Self-Management in Patients With Type 2 Diabetes: Protocol for a Pilot Randomized Controlled Trial

**DOI:** 10.2196/15709

**Published:** 2020-03-31

**Keywords:** motivational interviewing, diabetes, nurse, usual care, self-management, self-care

## Abstract

**Background:**

The nonpharmacological approach to diabetic control in patients with diabetes focuses on a healthy diet, physical activity, and self-management. Therefore, to help patients change their habits, it is essential to identify the most effective approach. Many efforts have been devoted to explain changes in or adherence to specific health behaviors. Such efforts have resulted in the development of theories that have been applied in prevention campaigns and include brief advice and counseling services. Within this context, motivational interviewing (MI) has proven to be effective in changing health behaviors for specific cases. However, stronger evidence is needed on the effectiveness of MI in treating chronic pathologies such as diabetes.

**Objective:**

This study will obtain preliminary data on the impact of a nurse-led MI intervention in improving glycemic control, as well as clinical, psychosocial, and self-care outcomes for individuals with type 2 diabetes mellitus when compared with usual care, with the aim of improving diabetic control in patients with diabetes.

**Methods:**

An open, two-arm, parallel, randomized controlled, pilot exploratory trial will be performed. Two government outpatient clinics in the New Territories West Cluster in Hong Kong will be involved. In total, 20 to 25 participants will be invited in each arm. Intervention participants will receive face-to-face MI interventions in addition to their usual care from the clinic. Control participants will only receive usual care. Outcomes are assessed at baseline, 6 months, and 12 months. The primary outcome measure is glycated hemoglobin levels. Secondary outcomes include blood pressure, BMI, hip and waist circumference, fasting blood, and psychosocial and self-care measures.

**Results:**

This study is currently underway with funding support from the Hong Kong College of Family Physician Research Seed Fund 2017.

**Conclusions:**

MI skills constitute the main strategies primary care nurses use on their patients. Having economical, simple, effective, and applicable techniques is essential for primary care professionals to help their patients change their lifestyle and improve their health. This study will provide scientific evidence on the effectiveness of MI. It will be performed with strict control over the data collection, ensuring the maintenance of therapeutic integrity.

**Trial Registration:**

Centre for Clinical Research and Biostatistics CUHK_CCRB00614; https://tinyurl.com/v9awzk6

**International Registered Report Identifier (IRRID):**

DERR1-10.2196/15709

## Introduction

### Background

Self-management of diabetes mellitus (DM) requires that patients can reconcile their resources and preferences with the standard therapeutic regimen for diabetes, a task that can be a challenging for many patients [1,2]. It has been widely accepted that diabetes education is not only required in the first few months following diagnosis, but is an important component of ongoing diabetes care because of the demanding self-care requirements, which requires multiple daily decisions to balance diet, physical activity, and medications [3]. There has been a keen interest in examining the impact that different kinds of patient education programs have on diabetes self-management. The findings of several meta-analyses from randomized controlled trials (RCTs) provide extensive evidence for the effectiveness of behavioral and educational intervention on fasting blood glucose and glycated hemoglobin (HbA_1c_). However, the long-term effects of such interventions are uncertain [4-11]. Knowledge about the effectiveness of behavioral and educational interventions on other diabetes-related outcome measures including blood pressure, lipid profile, body weight, self-management skills, health behavior, and psychosocial aspects are currently inconclusive [3,10-13]. There are few studies that have examined the impact of these psychological interventions among Chinese patients with diabetes. Critical assessment regarding the impact of behavioral and educational programs requires further research that is based on rigorous methods from high quality studies and are adequately powered as well as furnished with long-term follow-ups. The precise magnitude of the effectiveness should be examined, well-defined, and specific to the service recipients when designed [12-14].

Motivational interviewing (MI), described by Rollnick and Miller [15], is a well-defined and scientifically tested method of client counselling that has successfully been used to elicit and sustain a person’s behavior changes in a number of health care areas. A recent review of MI showed improvements in health behaviors such as diet and exercise in patients with diabetes [16]. However, studies on the effectiveness of MI have not been able to offer unanimous conclusions on clinical [17-23] and psychosocial attributes [18,21,24-27] in patients with diabetes. Previous reviews emphasize the need for studies of high methodological quality and adequate power to explore the effect of MI on glycemic control and well-being in patients with diabetes [14,16,28].

Given the fast pace of consultation flow in Hong Kong, where consultation time for a general practitioner is around 5 minutes for each patient in government outpatient clinics (GOPC), it is not possible for doctors to carry out MI. Management of diabetes involves a multidisciplinary approach in which allied health professionals such as dietitians, occupational therapists, and physiotherapists are also important team members. Our study will be novel as it is the first RCT using samples of Chinese patients with diabetes. In addition, we invited trained nurses to participate in our intervention.

### Knowledge Gap

Evidence-based MI research in various health care aspects is available abroad, but there is a dearth of such research in Hong Kong. It is important to build up local data on MI research.

### Objectives

This project aims to obtain preliminary data regarding the impact of MI on diabetes control compared with normal care among patients seen in primary care settings. The outcomes of interest include glycemic control (as measured by HbA_1c_), blood pressure, BMI, hip and waist circumference, fasting blood, and psychosocial and self-care measures.

The findings could inform the efficacy of MI for diabetes management in patients in family practices and contribute to better disease control.

## Methods

### Study Design

A pilot multicenter, parallel-group, RCT will be performed. It is an assessor-blinded study, involving two GOPCs in Hong Kong. They will be randomized with one allocated to an intervention group and the other to a control group.

Patients who attend the nurse-led clinic (NLC) in the intervention group will receive up to five individual counselling sessions based on MI in 1 year, in addition to their usual care.

A RCT design was chosen to minimize contamination between the control and intervention participants that could occur if participants in the same health service were randomized to different treatment groups. Furthermore, because the intervention will be targeted at changing the behavior of health professionals, once trained, treatment leakage could occur, as it will be difﬁcult for them to avoid using the intervention techniques with control participants.

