### Recruitment Procedure

The patients will be informed while participating in the NLC. Advanced practice nurses (APNs) will assist participants in achieving the primary goal of treatment for HbA_1c_ levels less than 7.0%, which is the target defined by the Manual for Risk Assessment and Management Programme (Diabetes Mellitus) in the Primary Care Setting under the Hospital Authority of Hong Kong. This primary goal is applicable for both groups in the study.

After randomization, all outcome measures will be assessed at baseline, 6 months, and 12 months in both groups. Randomization is generated by a research randomizer with a 1:1 allocation ratio in both groups. Each GOPC is considered as a single unit of randomization.

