### Sample Size Calculation

Sample size estimates were calculated using the ﬁxed number of clusters (2) available to the current study. The intracluster correlation coefﬁcient (ICC) accounts for the greater similarity of responses in patients within clusters compared with between clusters, and we could apply an ICC of 0.05 as typical in primary care settings [29]. The effect size for the primary outcome, HbA_1c_, was anticipated to be 0.32%, based on findings from a published meta-analysis [29]. Using these parameters, a sample size calculator for cluster-randomized trials [29] could estimate a total number of samples that would be required to achieve a power of 80%, while maintaining an alpha of 5% and a participant attrition rate of 20%.

However, since this is a pilot study, we will deploy a convenient sampling of 20 to 25 samples in each arm depending on resources. We anticipate performing a pragmatic cluster RCT in the future when resources are available so that sample size can be calculated with adequate power.

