### Statistical Analysis

Descriptive statistics will be used to summarize the characteristics of the GOPCs and participants with regard to baseline characteristics and patterns of mean change over time. The primary analysis will examine the changes in HbA_1c_ at the 6- and 12-month follow-ups in comparison to the baseline. Secondary analyses will include all clinical, psychosocial, and self-care measures that are continuous outcomes. For data analyses, SPSS (IBM Corp, Armonk, NY) will be used. As this is a pilot study, nonparametric statistical tests will be used. The baseline values will be reported as means (SD). A *P*-value<.05 will be regarded as statistically significant.

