## Discussion

### Impact

Demonstrating which of the two methods tested here is more effective can have a major impact on clinical practices when designing and proposing clinical protocols for the management of diabetes. Clinical interviewing skills and health education are the essential strategies used by nurses with their patients. Obtaining scientific evidence on the effectiveness of MI in primary care through strict monitoring of the training methods and controlling the integrity of the therapies applied will allow us to have economical, brief, effective, and applicable techniques to help patients change their health habits and achieve better health outcomes.

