### Conclusions

This study is one of the first attempts to assess the extent that the MI approach helps in overall diabetic care. The results obtained will help us understand the practical effectiveness of this approach, including its limitations and actual impact on Chinese patients with diabetes. If this method proves to be effective, our intention is to disseminate and promote that intervention used in APN sessions to promote better self-management.

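### With one clinic per arm, the MI effect is fully confounded with clinic, yet the protocol keeps an unreserved P<.05 rule and an effectiveness claim, and does not list the confounding as a limitation

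*Protocol article*

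**What the plan says.** All references are to the protocol article.

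- **Study Design:** two clinics take part. "They will be randomized with one allocated to an intervention group and the other to a control group". The study is labelled a pilot multicenter, parallel-group RCT.
- **Recruitment Procedure:** "Each GOPC is considered as a single unit of randomization". The computer-generated list under Stratification and Randomization orders the invitations to patients; it does not assign them to arms.
- **Sample Size Calculation:** confirms the "number of clusters (2) available to the current study", mentions an ICC of 0.05, settles on 20 to 25 patients per arm for reasons of resources, and leaves an adequately powered cluster trial to the future.
- **Hypotheses:** comparative, MI against usual care.
- **Statistical Analysis:** nonparametric tests of change in HbA1c from baseline. A P value below .05 "will be regarded as statistically significant". No reservation is made for clinic.
- **Abstract, Conclusions:** "This study will provide scientific evidence on the effectiveness of MI".
- **Impact:** "Demonstrating which of the two methods tested here is more effective can have a major impact on clinical practices".
- **Discussion, Conclusions:** "If this method proves to be effective, our intention is to disseminate and promote that intervention used in APN sessions".
- **Limitations:** small sample, dropout and questionnaire burden.

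**The concern.** Whatever differs between the two clinics during the year is part of the estimated MI effect. The protocol itself shows where differences can arise. Under Usual Care, each patient's own clinic reviews results, counsels, renews prescriptions and may refer for lifestyle counselling. Under Inclusion Criteria, patients may or may not already be on maximum oral treatment, so prescribing has room to diverge.

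The stated limitation is that a small sample makes significance harder to reach. The unstated one works in the other direction: ignoring clinic makes a false positive more likely. A reader who sees P<.05 could credit MI with what belongs to the clinic, and enlarging the sample within these two clinics would not help.

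**Working it through.** **1. Inputs.** From the protocol: 2 clinics, 1 per arm; m = 20 to 25 patients per arm, hence per clinic; ICC 0.05; significance at P<.05; anticipated HbA1c effect 0.32%. Assumed: two-sided testing; ICCs of 0.01 and 0.10 as a range; an HbA1c SD of 1.0 to 2.0 (step 5 only). There is no stated sample size or power to reproduce, because the Sample Size section lists inputs without a result.

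**2. Identifiability (no assumption needed).** Degrees of freedom for between-clinic variance = clinics − arms = 2 − 2 = 0. Two clinics can be allocated in only 2 ways, and these are mirror images, so a two-sided randomization P value is always 1.0.

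**3. Type I error of a test that ignores clinic.** If the analysed outcome has intracluster correlation ICC, the true variance of the difference in means exceeds the naive estimate by

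V = [1 + (m − 1) × ICC] / (1 − ICC).

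At ICC 0.05:
- m = 20: V = 1.95 / 0.95 = 2.05, √V = 1.43
- m = 25: V = 2.20 / 0.95 = 2.32, √V = 1.52

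The true error of a nominal 5% t test is 2 × P(T > t₀.₉₇₅ / √V) on 2m − 2 degrees of freedom. For m = 20 at ICC 0.05 the cut-off is 2.024 / 1.43 = 1.41, which gives 0.166.

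| ICC | m | √V | t test | Normal approximation, design effect only | Simulated Mann-Whitney (20,000 runs) |
|---|---|---|---|---|---|
| 0.01 | 20 | 1.10 | 0.073 | 0.072 | not run |
| 0.01 | 25 | 1.12 | 0.079 | 0.078 | not run |
| 0.05 | 20 | 1.43 | 0.166 | 0.160 | 0.155 |
| 0.05 | 25 | 1.52 | 0.193 | 0.186 | 0.184 |
| 0.10 | 20 | 1.80 | 0.266 | 0.250 | 0.257 |
| 0.10 | 25 | 1.94 | 0.306 | 0.288 | 0.289 |

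The Mann-Whitney column is the closest to the nonparametric tests that the protocol names.

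**4. More patients, same two clinics.** At ICC 0.05, m = 100 gives V = 5.95 / 0.95 = 6.26 and a t-test error of 0.43.

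**5. Clinic effect against the anticipated MI effect.** The clinic component alone gives the difference in clinic means an SD of √(2 × 0.05) × SD = 0.32 (SD 1.0) to 0.63 (SD 2.0) percentage points. With no MI effect, it would reach 0.32 in either direction with probability 31% (SD 1.0), 50% (SD 1.5) or 61% (SD 2.0).

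**The case against.** **It is a pilot, and the design is disclosed.** The aim is preliminary data, the unit of randomization and the number of clusters are stated, and a powered cluster trial is deferred. That stands as mitigation, and a two-clinic pilot is legitimate. But the Sample Size and Limitations sections present the shortfall as one of numbers, which does not touch confounding. Avoiding contamination is a reason to randomize clinics; it does not support an inference about effectiveness from one clinic per arm.

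**The clinics are alike.** They lie in one regional cluster and share eligibility criteria, HbA1c goal, routine check-ups and laboratory, and change from baseline removes stable differences in level. This may narrow the clinic effect. It does not remove differences in trend, and with one clinic per arm the data cannot show how large those are.

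**An analysis plan may specify the test.** A reader might infer that the protocol fixes a patient-level between-arm test. The Statistical Analysis section does not say so; that reading comes from the comparative hypotheses. If only within-arm change is tested, no comparative claim follows either. No unseen plan can separate clinic from arm.

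**The claims are modest.** A reader might infer that the protocol promises to show which method is better. The Impact section and the closing Conclusions do not go that far: both build conditionally on such a result. Only the Abstract's statement is flat. Nor is sample size the only limitation listed; dropout and questionnaire burden are there too.

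**Conclusion.** The point holds. Complete confounding of MI with clinic, and the absence of a valid standard error for the arm contrast, follow from the allocation alone and rest on no assumed ICC or SD. As written, the P<.05 rule cannot serve as a test of the comparative hypothesis, and the Abstract's effectiveness statement cannot be supported.

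The size is illustrative. A type I error of about 16 to 19% requires that an ICC of 0.05 apply to the analysed quantity and that the test ignore clinic. A reader might take those figures as the trial's actual error rate. The documents do not support that: the protocol offers 0.05 as a value typical of primary care and does not tie it to change in HbA1c, whose ICC could be lower or higher. Over ICC 0.01 to 0.10 the range is about 7 to 31%.

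**What to change.** 1. **Abstract (Methods) and Study Design:** describe the study as a pilot cluster trial with one clinic per arm.
2. **Statistical Analysis:** remove the P<.05 rule for between-arm comparisons and report the between-clinic difference descriptively. Label any interval as a sensitivity analysis under assumed ICCs of 0.01, 0.05 and 0.10, with the naive SE multiplied by √([1 + (m − 1) × ICC] / (1 − ICC)). For 20 to 25 per arm that is about 1.10 to 1.12, 1.43 to 1.52 and 1.80 to 1.94. State that this widens the interval but does not remove the confounding.
3. **Abstract (Conclusions), Impact and the closing Conclusions:** limit what the study can show to preliminary and feasibility data, and do not claim effectiveness of MI.
4. **Limitations:** add that clinic and arm coincide.

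The Results section says testing ended in mid-November 2019, so the allocation cannot change, but the analysis and claims can. The cost is wording and one short sensitivity calculation, with no added patients or procedures. The downside is that the stated claims become less favourable.

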### Subjects

#### Inclusion Criteria

Patients are eligible if they were diagnosed as having type 2 DM for at least 1 year and are 18 to 65 years of age with poor DM control (defined as HbA_1c_≥8). Patients who have or have not received maximum dosages of oral hypoglycemic agents are equally eligible.

#### Exclusion Criteria

Patients who are pregnant as well as those with severe debilitating diseases that preclude adherence to recommendations (eg, end stage cancer), cognitive deficits, or medical conditions rendering the individuals incapable of completing informed consent or participating in the study are excluded.

### Hypotheses

Our hypotheses are that MI can reduce HbA_1c_ levels, improve clinical and psychosocial outcomes, and increase diabetes self-care when compared with patients’ usual care.

### Recruitment Procedure

The patients will be informed while participating in the NLC. Advanced practice nurses (APNs) will assist participants in achieving the primary goal of treatment for HbA_1c_ levels less than 7.0%, which is the target defined by the Manual for Risk Assessment and Management Programme (Diabetes Mellitus) in the Primary Care Setting under the Hospital Authority of Hong Kong. This primary goal is applicable for both groups in the study.

After randomization, all outcome measures will be assessed at baseline, 6 months, and 12 months in both groups. Randomization is generated by a research randomizer with a 1:1 allocation ratio in both groups. Each GOPC is considered as a single unit of randomization.

### Sample Size Calculation

Sample size estimates were calculated using the ﬁxed number of clusters (2) available to the current study. The intracluster correlation coefﬁcient (ICC) accounts for the greater similarity of responses in patients within clusters compared with between clusters, and we could apply an ICC of 0.05 as typical in primary care settings [29]. The effect size for the primary outcome, HbA_1c_, was anticipated to be 0.32%, based on findings from a published meta-analysis [29]. Using these parameters, a sample size calculator for cluster-randomized trials [29] could estimate a total number of samples that would be required to achieve a power of 80%, while maintaining an alpha of 5% and a participant attrition rate of 20%.

However, since this is a pilot study, we will deploy a convenient sampling of 20 to 25 samples in each arm depending on resources. We anticipate performing a pragmatic cluster RCT in the future when resources are available so that sample size can be calculated with adequate power.

### Stratification and Randomization

Participants will be sampled by computerized random allocation software to achieve balance. The sampling procedure produces an ordered list of eligible participants. Then, recruiting ofﬁcers systematically invite eligible participants into the study. Once a participant declines participation, the recruiting ofﬁcer will move to the next person on the list. APNs will provide all participants an explanatory statement and consent form in person at their GOPC visit. Participant flow is shown in Figure 1.

**Figure 1 figure1:**
[figure not shown]
Trial participant flow. DM: diabetes mellitus; HbA_1c_: glycated hemoglobin.

### Usual Care

Medical treatment is not a part of the intervention. All participants, irrespective of participation in the intervention group or the control group, will undergo the same routine check-up at the GOPC in charge of their diabetes care. Biochemical tests and examinations will be performed during these visits in accordance with protocols.

Individual counselling and recommendations will be given based on the results of the examinations, biochemical tests, and self-monitoring of blood glucose. Renewal of prescribed medication will also be done at these check-up visits. Patients could be referred to individual counselling for diet modification, optimization of physical activity, smoking cessation if applicable, and minimization of alcohol use if required by their usual health care provider.

### Research Intervention

The theoretical approach of the intervention is based on the self-efficacy theory and MI spirit. Perceived self-efficacy is defined as people’s beliefs about their capabilities of producing designated levels of performance on exercising influence over events that affect their lives [30]. MI is used as a method to facilitate this process and is a directive counselling style for eliciting behavior change by helping patients to explore and resolve ambivalence [31,32]. In addition to their usual care, patients in the intervention group will receive a 1-year MI program consisting of up to five individual counselling sessions lasting approximately 30 to 45 minutes. Each participant in the intervention group is assigned an APN who has received training in MI. The style of the interview is standardized with the following components: seeking to understand the person’s frame of reference; expressing acceptance and affirmation; eliciting and selectively reinforcing the client’s own self-motivational statements of problem recognition, concern, desire and intention to change, and ability to change; exploring the client’s degree of readiness to change; and affirming the client’s freedom of choice and self-direction. Exploring readiness to change is used as a component of the therapeutic process and not an outcome. Each session follows a semistructured MI format, specifically developed for this intervention program. Participants may bring up any concerning issues related to diabetes self-care during the intervention sessions. The participants in the intervention group may be referred by the health care professional to individual counselling for lifestyle modification, which may include dietary changes, promotion of physical activity, and counseling on quitting smoking and minimizing alcohol consumption.

